### *6.2 Medication(s)/treatment(s) permitted (including rescue medication) and not permitted before and/or during the trial*

Participants are not precluded from enrolling in other studies concurrently.

### *6.3 Procedures for monitoring subject compliance*

Not applicable

## Section 7 – Assessment of Efficacy

### 7.1 Specification of the efficacy parameters.

#### *Primary outcome:*

Any adverse drug event within 30-days of hospital discharge (as defined by a 5 or 6 on the Leape and Bates scale).

#### *Secondary outcomes(s):*

- **Proportion of patients with one or more PIM discontinued at discharge:** determined from the discharge prescription as compared to the best possible medication history performed on admission (medication reconciliation). Medications which have been deliberately tapered to lower doses at discharge will be classified based on a blinded expert review as to whether they constitute “deprescribing”.
- **Absolute number of medications at discharge:** determined from the discharge prescription.
- **Absolute number of PIMs at discharge:** once discharged the MedSafer algorithm will be run on the discharge medication list and PIM status recorded.
- **Adverse drug withdrawal events within 30-days post discharge:** this constitutes a subclass of adverse drug event whereby the adjudicator believes that the patient suffered an adverse event as the consequence of stopping, holding, omitting, decreasing or deprescribing a medication.
- **Absolute number of medications at 30 days post-discharge:** determined from post-discharge interview and review of medications.
  - **Proportion of medications that remain deprescribed at 30 days post-discharge:** determined by asking patients if they have restarted medications which were classified as being deprescribed at discharge.
- **Adverse events within 30-days post discharge:** determined by review of the post-discharge interview.
  - **30-day readmissions (ER or hospitalization) within 30-days post discharge:** a subset of adverse events related to emergency room visit or unplanned readmission to hospital. Details abstracted from the admission note and the death certificate/discharge summary.
  - **30-day mortality in those that survive to hospital discharge:** a subset of adverse events related to death (either in hospital or not in hospital). Where patients have died out of hospital, a modified interview of next of kin will be performed to obtain basic details about the death and this will be adjudicated. Where patients have been readmitted prior to death,
  - **Falls within 30-days of hospital discharge:** based on patient self report at the discharge interview.
- **30-day post-discharge sleep questionnaire responses:** as assessed from the patient interview using the questionnaire.
- **30-day self-reported health-related quality of life:** as assessed from the patient interview using the questionnaire.

*Sensitivity analyses:* Adverse drug events as defined by a 4,5 or 6 on the Leape and Bates scale

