In the control arm, all eligible participants will receive medication reconciliation at admission and discharge (current standard of care), and a structured follow-up phone interview to determine if they had an adverse event and adverse drug event within 30-days of hospital discharge. A prioritized deprescribing list will NOT be generated for patients during the control period of the study although the potentially inappropriate medications and any standard of care deprescribing decisions will be recorded.

During the intervention period, the medical teams will receive a printout with individualized and prioritized deprescribing opportunities: a) identifying the medication, b) explaining (with references and rationale) why that medication is potentially inappropriate and c) instructions on how to safely stop/taper the medication and what to look out for post discontinuation. The treating medical team will review these opportunities with the unit pharmacist and patient and subsequently appropriate candidate medications for deprescribing could be tapered or stopped by the most responsible physician on the CTU.

During the intervention period, for all patients who give consent for follow-up, the research assistants will provide a generic deprescribing brochure to inform them of the relevance of the study and the importance of medication review. Additionally, for those patients who are taking a proton pump inhibitor or a sedative hypnotic, they will receive corresponding patient-oriented educational material. The purpose of these brochures is to educate patients about the harmful effects of PPIs and sedative hypnotics. The patient brochures have been independently designed by the Canadian Deprescribing Network with input from patient stakeholders and the information is presented in lay terms in both French and English. Copies of each of the brochures are available online.

Proton pump inhibitors: <http://www.criugm.qc.ca/fichier/pdf/PPI-EN-Men.pdf>

Sedative hypnotics/sleeping pills: <http://www.criugm.qc.ca/fichier/pdf/BENZOeng.pdf>

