Participants will be phoned within and around 30-days post discharge (day 28-35) and they will have a structured interview to determine their current medication regimen and if it has changed, along with any contact (planned or unplanned) with the healthcare system, and any new or worsening conditions. They will also have the opportunity to report on their quality of sleep (Patient-Reported Outcomes Measurement Information System Sleep Disturbance Form 4a) and quality of life (EQ-5D-5L). All information will be collected in an electronic case file report for later blinded adjudication by an expert in pharmacy, geriatrics, or general internal medicine.

At the time of consent, we will also request access to provincial health insurance data up to one-year post hospital discharge in jurisdictions where available for use in subsequent analyses.

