c. **Medication history**

- The **Admission** column on the left shows the medication and dosage the patient was taking prior to admission.
- The **Discharge** column shows what action (continued, modified, stopped) was taken with these medications at the time of discharge from the hospital (from med reconciliation).
- The **Interview** column contains changes in meds between discharge and the time of the interview, including medications stopped, restarted, or newly started post-discharge.

- If a medication was continued, it will remain **green** in each column (*see clopidogrel*).
- If a medication was modified at discharge from the hospital, the medication will be **orange** in the **Discharge** column. *Note that for a medication change at discharge, you will need to read the new dosage to see if it is an increase or decrease. The field that was modified will be indicated in bold.* If the medication in the interview column is green, this means it was continued at the modified discharge dose (*see nitroglycerin*).
- If the medication was modified following discharge, the medication will be **orange** in the **Interview** column. The arrow will indicate if this is an increase or decrease from discharge (*see ciclesonide*).
- If a medication is stopped at discharge, it will no longer appear in that column (*see pantoprazole*).
- If a medication was stopped post-discharge, this will be indicated in **red** (*see tamsulosin*).
- For changes recorded by the interviewer, by who, when and why the change was made will be indicated if applicable.
- Medications started at discharge from the hospital that were not taken prior to admission will not appear in the Admission column (*see acetaminophen*).
- medications that were started after the discharge from hospital will appear in **yellow**. If available, the information regarding why and when it was prescribed will be indicated (*see finasteride*). If no reason for starting could be elucidated from the interview it will say “none”
- Reminder: If a short-form interview was completed by the RA for a 30-day readmission, the medications in the Interview column represent the actions taken by the team at the time of readmission.

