A generalized linear regression model will compare the number of medications at 30-days post discharge controlling for intervention, time period, and the number of baseline medications as fixed effects and cluster as a random effect. This analysis will be conducted on patients who have consented to, and participated in, the post-discharge follow-up.

- Absolute number of PIMs at discharge

A generalized linear regression model will compare the number of PIMs at discharge controlling for intervention, time period, and the number of baseline PIMs as fixed effects and cluster as a

random effect. This analysis will be conducted on all patients who are discharged alive on a study unit (see above re transitions of care).

- Proportion of medications that remain deprescribed at 30 days post-discharge

For drugs which were deprescribed at discharge, the proportion which remained prescribed at 30-days (without resuming) will be given for the control and intervention periods without statistical testing. This analysis will be conducted on patients who have consented to, and participated in, the post-discharge follow-up.

- 30-day post-discharge sleep questionnaire responses (Patient-Reported Outcomes Measurement Information System Sleep Disturbance Form 4a)

For individual elements of the score, the number and proportion of each response will be presented in tabular form for pre-hospital and post-hospital results, stratified by intervention for all respondents. The total score will be transformed to a T-score using the standardized table for adults and the median T-scores and interquartile ranges will be presented in tabular form for those respondents who completed both questionnaires and will be stratified by intervention. The Wilcoxon matched pairs sign rank will be used to compare prehospital scores to post discharge scores within intervention and control respectively.

- 30-day self-reported health-related quality of life (EQ-5D-5L and Visual Analog Scale)

Among those who complete the post discharge interview and who are able to provide responses to the EQ-5D-5L questionnaire, the raw scores will be converted into estimates of quality of life using a validated Canadian time-trade off value set. They will be tabulated with median values and interquartile ranges along with the median and IQR for the visual analog scale. A simple comparison between the intervention and control for these measures will use Wilcoxon rank sum.

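### A dose reduction can count as deprescribed at discharge, but the 30-day persistence rule has no dose criterion, so a partial taper that is raised again is scored as still deprescribed

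*Protocol*

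**What the plan says.** Two definitions in the protocol's Section 7.1 (secondary outcomes) meet here. Under the outcome on discontinuing potentially inappropriate medications (PIMs) at discharge, the text reads: "Medications which have been deliberately tapered to lower doses at discharge will be classified based on a blinded expert review", the question for that review being whether the reduction amounts to deprescribing. A drug still in use at a lower dose can therefore enter the set of deprescribed drugs. Under the outcome on deprescribing that lasts to 30 days, status is "determined by asking patients if they have restarted medications which were classified as being deprescribed at discharge".

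The matching entry in Section 9.1a reads: "For drugs which were deprescribed at discharge, the proportion which remained prescribed at 30-days (without resuming) will be given". The results "will be given for the control and intervention periods without statistical testing".

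Three other places bear on the point:

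- Section 2.2: in the intervention period the printout carries "instructions on how to safely stop/taper the medication and what to look out for post discontinuation". No such list is produced in the control period.
- Section 6.1: the follow-up call is a "structured interview to determine their current medication regimen and if it has changed".
- Section 7.3, Adjudication Manual, Medication history: for a drug modified after discharge, "The arrow will indicate if this is an increase or decrease from discharge".

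**The concern.** The entry rule and the exit rule do not match. A drug can become deprescribed in two ways, by being stopped or by an accepted dose reduction. It can lose that status in only one way, by being restarted. For a partial taper that was never completed, a patient whose dose has gone back up can truthfully say that the drug was not restarted, and the reversal goes uncounted.

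At stake is the outcome that speaks most directly to whether deprescribing lasts beyond discharge. For partial tapers the error runs one way, because nothing in the rule offsets a missed reversal. It could also fall unequally on the two periods, since taper instructions are issued only in the intervention period.

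**Working it through.** The protocol states no figure for this outcome, so there is nothing to reproduce. The check sets the rules side by side and then puts the size in symbols.

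**Step 1: which states the rule can score.**

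| Status at discharge | Event by the interview | Score under the rule as written |
|---|---|---|
| Stopped | Not restarted | Remains deprescribed |
| Stopped | Restarted | Reversed |
| Accepted taper, later completed to zero | Restarted | Reversed |
| Accepted partial taper, still taken | Dose unchanged or lower | Remains deprescribed |
| Accepted partial taper, still taken | Dose raised again | Remains deprescribed |

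Only the last row is wrong.

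**Step 2: whether *restarted* can be read to include a dose increase.** The Medication history section of the Adjudication Manual names restarting as one kind of post-discharge change, next to stopping and new starts. It handles modified doses separately, with their own colour and arrow. In its sample table, furosemide goes from twice daily to once daily at discharge and is continued at that level. Had it gone back to twice daily, the file would show an increase, not a restart. The protocol's own vocabulary therefore keeps the two apart.

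**Step 3: size.** Let

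- t = share of deprescribed drugs that are accepted partial tapers,
- r = share of those whose dose is raised again by the interview,
- p = share of all other deprescribed drugs that are not restarted.

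Persistence with reversed tapers counted as reversed: (1 − t)p + t(1 − r).

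Persistence under the rule as written: (1 − t)p + t.

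Overstatement: the difference, t × r. It does not depend on p.

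The documents give neither t nor r. Assumed for illustration only, t = 10% to 30% and r = 10% to 40%:

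- low end: 0.10 × 0.10 = 0.01, or 1 percentage point;
- high end: 0.30 × 0.40 = 0.12, or 12 percentage points.

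**Step 4: comparison between periods.** The distortion of the difference (intervention minus control) is t₁r₁ − t₀r₀. It is zero if the products are equal. If each product lies anywhere in the assumed 1 to 12 points, the distortion lies between 1 − 12 = −11 and 12 − 1 = +11 points. The documents fix neither its sign nor its size. Taper instructions given only in the intervention period make t₁ > t₀ plausible, but nothing is said about r₁ against r₀.

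**Step 5: the wording of Section 9.1a.** The sentence says *prescribed* where the item's own heading, Section 4.1 and Section 7.1 all say *deprescribed*. The bracketed condition about not resuming fits only the latter.

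**The case against.** The strongest reply is that the protocol nowhere says a reversed taper counts as persistent. Not resuming could be read as not resuming the earlier dose, the interview covers the whole regimen and any change to it, and the coding of such cases could be left to a separate analysis plan. Part of this stands: the scoring follows from the literal wording and is not announced as such. But Section 9 is itself headed as the statistical analysis plan, it states the criterion for this outcome, and the manual separates restarts from dose increases. This is a stated rule that gives a wrong answer for one kind of drug. At the least, two analysts could score the same drug differently.

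It can also be said that the 30-day medication count gives independent evidence of durability. That is true for stopped drugs. A count does not register dose, so it does not cover re-escalated tapers.

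Several stronger readings are tempting, and the documents do not support them:

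- *A taper can only be scored a success.* A taper completed to zero and then restarted is a failure under the written rule. Reductions also enter only if the blinded review accepts them, and it may accept few.
- *Section 9.1a reports the opposite quantity.* Its heading and bracketed condition show a slip of one word.
- *Tapered drugs count as deprescribed while still counting as PIMs on the discharge list.* Section 7.1 says only that the algorithm is run on that list. Whether its rules depend on dose is not shown.
- *The discharge outcome should be limited to full stops.* That is a preference. The protocol plans a blinded review of dose reductions, and the tool treats reducing a drug as a deprescribing action.

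**Conclusion.** The point holds in a limited form. The persistence rule lacks a dose criterion for drugs that became deprescribed by dose reduction, so a partial taper that is raised again is scored as lasting. The overstatement is t × r, which is 1 to 12 percentage points under assumed inputs that have no source in the documents.

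A reader might infer that the trial's persistence result is biased in favour of the intervention. The documents do not establish that. It requires the product t × r to be larger in the intervention period, which is plausible but not shown.

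Importance is minor. This is a sub-item among the secondary outcomes, reported descriptively without a test. The primary outcome, the sample size and the modelled comparisons are untouched. The data needed are largely in hand, so the fault lies in the outcome definition and not in data capture.

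**What to change.** In Sections 7.1 and 9.1a, define persistence by the way the drug became deprescribed:

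1. Stopped drugs: persistent if not restarted by the 30-day interview.
2. Dose reductions accepted as deprescribing: persistent if no increase from the discharge dose is recorded at the interview and, where the taper was completed, the drug was not restarted.
3. Report the proportions for stopped and tapered drugs separately, by period, with the number of drugs in each.
4. In Section 9.1a, correct *prescribed* to *deprescribed*.

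Score item 2 without knowledge of the period, as is already done for tapers at discharge. State how drugs are scored when only the short-form interview at readmission exists, since the interview column then shows the readmitting team's actions.

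The rule should rest on the direction of change, not on a return to the admission dose. In the manual's sample table, a drug modified after discharge shows the direction and reason but no new dose, so a return to the admission dose may not be recoverable.

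Cost: wording and programming, with no new data collection. Reported persistence may be slightly lower, and a partial increase that stays below the admission dose will count as reversed. Section 9.1b describes post-hoc analyses in the past tense, so analysis appears to have been done already. The change should therefore be recorded as a clarification or deviation under Section 9.6.

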## 7.2 Methods and timing for assessing, recording, and analysing efficacy parameters.

Post-discharge interviews will be performed by trained research staff and will use a standardized questionnaire to obtain the information necessary to help determine if an adverse event has occurred and obtain an estimate of the patient's sleep quality and post-discharge health-related quality of life.

These post-discharge surveys will be combined with patient demographics into a de-identified record as soon as the telephone interview has been completed. Trained adjudicators will review these records and determine if an adverse (drug) event occurred post-discharge.

We will also, with consent, collect data on prescribed medications, hospitalizations and medical services that any eligible participant receives 12 months prior to their enrolment in the study, during their hospital admission at the time of enrolment, and up to 12 months after their hospital admission. Subsequently, when sufficient funding is available and/or provincial access pathways are clarified we will perform a pre-planned secondary analysis on those with long-term administrative data.

Patients will have the option of consenting for both the telephone interview and access to medication and hospitalization data for up to 1-year post-discharge, data access only, or interview only.

## 7.3 Methods for adjudicating adverse drug events:

### *Summary*

We use a modification of the Leape and Bates method. First the adjudicator reviews the file and decides if any adverse event has happened. If not, the review is complete. If yes, the reviewer assigns a score based on the Leape and Bates scale with 5 and 6 representing ADE. The reviewer then identifies which events they believe represent the adverse event and, if ADE, which drugs they believe may or may not have been revised. If there is an ADE identified, the reviewer also rates whether it may have represented an adverse drug withdrawal event.

Each file is randomly assigned to 2 reviewers. In the event of a disagreement as to adverse event occurrence or adverse drug event occurrence, a third reviewer is randomly selected (and is blinded and independent to perform a third review).

Adverse drug events and adverse events are those which were categorized as such by 2 or more reviewers under the above process.

## Adjudication Manual:

Log onto MedSafer trial application using Chrome-based browser/

1. Once logged on, select Reviewer role in the top left corner of the page.

[figure not shown]

2. You will be able to see a list of patients assigned to you for adjudication. You can keep track of your patient if needed by noting the Review ID.
3. Click on the Orange icon with a hammer to begin the adjudication for a given patient.

| Review ID | Adjudication                                                                       | Flag for review |
|-----------|------------------------------------------------------------------------------------|-----------------|
| 2611      | [figure not shown]  | True            |
| 8077      | [figure not shown]  | True            |
| 2602      | [figure not shown] | False           |

4. In the first section, you will see the patient's demographic information such as: age, sex, reason for admission, frailty, GFR, living arrangements prior to admission, discharge location, readmissions to ER/hospital (if applicable), death details (if applicable) and interviewer notes (if applicable). There is a scrambled patient ID so you cannot tell the site nor the intervention status. **The following screenshots are simulated patient data and do not constitute a real patient.**

**a. Conditions**

This section shows new or worsening conditions reported by the patient since discharge.

Conditions

| Condition | New/Worse Condition
(Interview) | Details                                                                                                             | Days Post Discharge | How long did it last? | Adverse
Event                             | ADE                                               |
|-----------|------------------------------------|---------------------------------------------------------------------------------------------------------------------|---------------------|-----------------------|----------------------------------------------|---------------------------------------------------|
| pneumonia | Worse                              | problem breathing,
went to the ER where
he was initially told he
had an infection. was
in the ER 2 days | 29                  |                       | Adverse
Event
 | Adverse Drug
Event
 |

642  
643  
644

